### Data processing and analysis

We will enter data into Excel™ software and analyze it using Stata™ software. Descriptive statistics will summarize continuous data, such as the mean, median, standard deviation, and interquartile range. We will use frequencies and percentages to summarize categorical data. Multiple statistical tests and methods will be employed. The univariate analysis will typically utilize Pearson’s chi-squared correlation or Fisher’s exact test, where appropriate. As for the primary outcome (mean difference in the viral load of HIV-positive children with VLS), we will use an independent *t*-test to compare the means of participants in the intervention and control arms. We will develop a multivariable regression model, adjusting for clustering and other confounders for potential confounding. We will use proportions and tests for different proportions as measures of improvement using the difference in difference. All statistical tests will be two-sided and *P* < 0.05 will be considered statistically significant.

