### Outcome measures

The study will have two outcome measures. The primary measure will be the adherence, this will be measured by using the standard adherence tool (National AIDS Control Program [32]) and loss to follow-up (retention in CTC), which will be compared in both arms. We will measure these metrics at baseline, subsequent follow-up, and the study’s end (i.e. 6 months). The secondary measure will be the viral load, which will be measured at the baseline and subsequently at the 6-month study’s end, comparing both arms.

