### Sample size calculation and selection

The trial will be conducted in 20 CTC clinics that deliver HIV care and treatment within the four selected districts (10 CTCs will carry out the intervention and 10 CTCs will carry out standard care). We determined the study size from the primary outcome of proportional HIV-positive children with a viral load >1000 copies/ml. According to THIS (2018), 18% of HIV-positive children under the age of 15 years had a viral load >1000 copies/ml; thus, we assumed that value for standard care. Therefore, under a cluster design, the study will need a total sample size of about 268 children (134 in the intervention group and 134 in the control group) to increase the proportion of children with viral suppression from 18% to 30% with 80% power, ata5% significance level, an intra-cluster correlation of 0.01, and 10% expected loss to follow-up. We carried out this power calculation using the Stata™ function “clustersampsi” command (clustersampsi, binomial p1[0.18] p2[0.3]k[20] rho[0.01] alpha[0.05] beta[0.8]).

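### No test is consistently named as confirmatory, yet every test is judged at two-sided P < 0.05; on either reading of the primary outcome the false-positive chance can be about 8-10% rather than 5%

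*Protocol article*

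**What the plan says.** All references are to the protocol article.

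- **Decision rule (Data processing and analysis).** "Multiple statistical tests and methods will be employed", and then "All statistical tests will be two-sided and *P* < 0.05 will be considered statistically significant". No test is exempted or ranked by this rule.
- **Outcome measures.** "The primary measure will be the adherence, this will be measured by using the standard adherence tool", joined to "loss to follow-up (retention in CTC), which will be compared in both arms". Viral load is called secondary here. Nothing says whether one or both parts of the primary measure must show an effect.
- **Abstract, Sample size calculation and selection, and the text after Figure 1.** All three treat viral load relative to 1000 copies/ml as the primary outcome, that is, a proportion.
- **Data processing and analysis again.** Here the primary outcome is a mean difference in viral load, compared by an independent t-test. The same section adds Pearson chi-squared or Fisher tests, a multivariable regression adjusting for clustering, and tests of proportions using a difference in difference.
- **Sample size.** The trial is sized "to increase the proportion of children with viral suppression from 18% to 30% with 80% power" at a 5% significance level, which is one test of one proportion.

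**The concern.** The 5% in the sample size section is the error rate of one comparison. The blanket rule applies the same 5% to each of several comparisons, and the sections give three different answers to which of them is primary.

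Deciding which outcome is primary would not by itself restore a single test:

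- If the adherence and retention pair is kept, two separate comparisons remain with no success criterion.
- If viral load is kept, a comparison of proportions and a comparison of means remain, with a regression besides.

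A reader of the results could not tell which P value was meant to carry the conclusion that the Konga model works. The investigators could choose after seeing the data without departing from the text.

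**Working it through.** **Inputs from the document.** Each test is at two-sided 0.05 (Data processing and analysis). One test at 5%, 134 children per arm, 10 clinics per arm, intra-cluster correlation 0.01, 10% loss, 18% suppressed under standard care (Sample size calculation and selection). Viral load above 1000 copies/ml at entry (Study design and population; Recruitment).

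**Inputs assumed.** The number of tests counted, their correlation, 60% adherent, an adherence-viral load correlation of 0.2-0.5, and the viral load distribution (raw or log scale). The document gives none of these.

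**The plan's own figure.** The plan gives no overall error rate. Its only figure is 5% for a single test: 1 - 0.95^1 = 5%.

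**Step 1: adherence and retention.**
- Either one suffices, independent tests: 1 - 0.95^2 = 9.75%, about 9.8%.
- Either one suffices, simulated with no true effect (8,000 runs per setting, 134 per arm, 10% lost, children independent so that only multiplicity is measured): 9.6-10.1%.
- Both must succeed, independent tests, no effect on either: 0.05 × 0.05 = 0.25%. Whatever the correlation, this rule cannot exceed 5%.

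So the unstated success criterion decides whether there is any inflation.

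**Step 2: viral load tested two ways.**
- Upper limit for two valid 5% tests, whatever their correlation: 2 × 5% = 10%.
- Simulated as above, suppression proportion or mean viral load: 8.0-8.7%.
- A second null simulation (6,000 runs, 268 children in 20 clusters) added a cluster-level test of suppression, making three viral-load tests: 9.2-9.3% at intra-cluster correlation 0, and 9.3-10.0% at 0.01.

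The 0.01 figures include some error from the chi-squared and t-tests ignoring clustering.

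**Step 3: all four tests as one family** (adherence, retention, suppression, mean viral load).
- Independent: 1 - 0.95^4 = 18.5%.
- Equal correlation between test statistics: 17.3% at 0.3, 15.6% at 0.5, 11.5% at 0.8.
- Simulated without clustering: 16.6-17.5% in the first simulation, 16.7-17.3% in the second.

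**Step 4: does a difference in difference of suppression add a test?** All children enter above 1000 copies/ml. Taking the entry value as baseline, suppression is 0% in both arms at the start. With p1 and p0 the 6-month proportions suppressed, the difference in difference is (p1 - 0) - (p0 - 0) = p1 - p0. That is the 6-month comparison itself and adds no separate chance of error.

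**Step 5: after the fix.** One named test gives 5%. In a fixed sequence, each later test is made only if the one before it is significant, so the overall error stays at 5%. This requires every test in the sequence to be valid under clustering.

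**The case against.** **The protocol does rank outcomes and does name a primary test.** Outcome measures separates primary from secondary, and Data processing and analysis attaches a t-test to the primary outcome. This stands: a reader might infer that there is no order and no primary test at all, and that is too strong. But the designations contradict one another, so none of them fixes the confirmatory test.

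**A larger error is tempting.** One might conclude that the true error is about 17-20%. The document does not support that. About 17% needs adherence, retention, suppression and mean viral load pooled into one confirmatory family, and no section defines such a family. A secondary outcome reported at 5% does not raise the error of the primary one. Reaching 20% takes a fifth test, such as a difference in difference on adherence, which the protocol does not specify; on suppression it adds nothing (Step 4).

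**No success rule is stated.** The text says only when a result counts as statistically significant, not that any one such result proves the intervention. This stands, so the 8-10% is conditional on that use. Nothing in the protocol rules it out.

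**The t-test may be a different one.** The wording can be read as confined to children who reach suppression. The simulated test used all followed children. The 10% upper limit for two valid 5% tests holds on either reading.

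**An article may leave multiplicity to an analysis plan.** The absence of an alpha split is therefore not the point. The point is that the article states a blanket rule and gives conflicting answers to which outcome and test are primary.

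**The remedy takes a side on the primary outcome.** True. It follows the outcome on which the sample size was calculated and which the Abstract and the text after Figure 1 also name.

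**Conclusion.** The point holds in a limited form. The protocol has no consistently designated confirmatory test, while every test is judged at two-sided 5%. If any one significant result were taken as success, the false-positive chance would be about 10% for adherence and retention (9.8% if independent) and about 8-10% for viral load tested two ways, against the 5% assumed in the sample size. That is up to roughly double the nominal rate. If both parts of the primary measure had to succeed, there would be no inflation on that reading.

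The 17-18% figure applies only if all four tests were treated as one family, and should not be quoted as the trial's error rate. All simulated figures depend on assumed correlations, adherence and viral load distributions. The defect should be corrected before outcome data are examined; it does not by itself invalidate the trial.

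**What to change.** In Outcome measures and in Data processing and analysis:

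1. Name one confirmatory test at two-sided 5%: the cluster-adjusted comparison between arms of the proportion below 1000 copies/ml at 6 months, the outcome used for the sample size.
2. Make adherence and retention secondary. Test them in a pre-stated order, for example 6-month adherence and then 6-month retention, each at 5% with cluster-adjusted methods, and only if the test before is significant.
3. Report the t-test, the chi-squared or Fisher tests, the difference in difference and other regressions as supportive, with estimates and confidence intervals and no separate claim of significance.
4. Confine the blanket P < 0.05 sentence to the tests in items 1 and 2.

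The cost is a few sentences. It needs no more children and no more data, and the first test keeps the full 5%. The small downside is that an effect on adherence or retention could not be claimed as confirmed if suppression is not significant.

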## Abstract

This study aims to test the effectiveness of a community-based intervention (Konga model) to improve viral-load suppression in children living with human immunodeficiency virus (HIV) and enrolled in care and treatment centers in Tanzania mainland. The study will be a cluster-randomized clinical trial study designed with both intervention and control arms. The study will involve 268 children with a viral load of >1000 copies/ml who are aged between 2 and 14 years. The children will be randomly allocated into the intervention and control arms. The intervention will include three distinct activities: adherence and retention counseling, psychosocial support, and comorbidity screening (i.e. tuberculosis). The outcome of the study will be assessment of the success of the intervention to increase medication adherence with the immediate result of reducing the viral load below 1000 copies/ml. Descriptive statistics will be used to calculate the mean, median, standard deviation, and interquartile range of continuous data. We will use frequencies and percentages to summarize categorical data. As for the primary outcome (proportion of HIV-infected children with viral suppression), we will compare the proportion of successful participants in the intervention and control arms. Proportions and tests for different proportions will be used as a measure of improvement. All statistical tests will be two-sided and *P* < 0.05 will be considered statistically significant.

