### Measurement of variables

#### Dependent variable

The dependent variable will be the viral load cell count and it will be classified as suppression when the count is <1000 copies/ml and unsuppressed when >1000 copies/ml.

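### The analysis section ties the primary outcome to a t-test of mean viral load in children with VLS, which conflicts with the suppression proportion the trial is sized on and, read literally, selects on the outcome

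*Protocol article*

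**What the plan says.** The protocol article describes the primary outcome in three incompatible ways.

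- **Mean viral load.** Data processing and analysis opens the key sentence with "As for the primary outcome (mean difference in the viral load of HIV-positive children with VLS", names an independent t-test, and says its purpose is "to compare the means of participants in the intervention and control arms".
- **Proportion suppressed.** The Abstract uses nearly the same sentence with a different outcome: "As for the primary outcome (proportion of HIV-infected children with viral suppression), we will compare the proportion of successful participants". The sample size is set "to increase the proportion of children with viral suppression from 18% to 30" (percent). The Dependent variable section makes viral load binary: "it will be classified as suppression when the count is <1000 copies/ml". The text under Selection and randomization of CTC also gives a viral load below 1000 copies/ml as the primary outcome.
- **Adherence and retention.** Outcome measures makes these primary and viral load secondary.

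Data processing and analysis contains two further statements: "We will develop a multivariable regression model, adjusting for clustering and other confounders for potential confounding" and "We will use proportions and tests for different proportions as measures of improvement using the difference in difference". Neither is linked to the primary outcome, and the regression sentence names no outcome.

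Study design and population and Recruitment both require a viral load above 1000 copies/ml at entry.

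**The concern.** VLS is the article's abbreviation for viral-load suppression, and suppression means fewer than 1000 copies/ml. No child meets that at entry, so children with VLS can only be those who reached it during follow-up. Comparing mean viral load within that group has three consequences:

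- All treatment failures are dropped.
- The two groups compared are formed by a post-randomisation event, so randomisation no longer protects the comparison.
- Only values under the threshold are examined, where a change in how many children cross it hardly shows.

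The looser reading, all participants, avoids the selection but not the mismatch. The trial would be sized on a binary outcome and tested on a continuous one, with a t-test that ignores randomisation by clinic. Since the article supports several primary tests, the choice among them could be made after results are seen.

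**Working it through.** **Inputs from the article:** 134 children per arm; 10% loss; suppression 18% versus 30%; 10 CTCs per arm; intra-cluster correlation 0.01; two-sided 5%; 80% power. The article gives no mean or SD for viral load, so any power figure for a t-test rests on an assumed distribution.

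**1. The plan's own figure.** The pooled two-proportion formula gives 198 per arm before clustering, and the unpooled one 195. For 10 clusters per arm the cluster size is m = n(1 − ρ)/(k − nρ).
- Pooled: 198 × 0.99/(10 − 1.98) = 24.44 per CTC, so 244.4 per arm; 244.4/0.9 gives 272 per arm, 544 in total.
- Unpooled: 195 × 0.99/(10 − 1.95) = 23.98 per CTC, so 239.8 per arm; 239.8/0.9 gives 267 per arm, 534 in total.

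The stated total of 268 is not reproduced. It is close to the per-arm requirement.

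**2. Who enters the t-test on the literal reading.** Evaluable per arm: 134 × 0.9 = 120.6.
- Control: 0.18 × 120.6 = 21.7.
- Intervention: 0.30 × 120.6 = 36.2.
- Share left out: 1 − (0.18 + 0.30)/2 = 76%.

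This count uses only the plan's figures.

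**3. What that test can detect, ignoring clustering.** The standardised difference detectable with 80% power is (1.96 + 0.84) × √(1/21.7 + 1/36.2) = 0.76 SD.

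**4. How often it rejects if suppression really is 18% versus 30%.** Simulated with 121 per arm, no clustering:

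| Assumption | Suppressed children only | All children |
|---|---|---|
| Suppressed children have the same viral-load distribution in both arms | 5.3% | proportion test about 60% |
| Whole log10 distribution shifts, normal, SD 1 | 8.8% | log10 t-test 86% |
| Same shift, SD varied from 0.7 to 1.2 | 8.7% to 9.6% | log10 t-test 85% to 87%; raw-scale t-test 16% to 42% |

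In the first row the restricted test rejects at its null rate although the true difference in suppression is 12 percentage points. Simulation error is about half a percentage point on the restricted figures.

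**5. Clustering.** With 120.6/10 = 12.06 evaluable children per CTC, the design effect is 1 + (12.06 − 1) × 0.01 = 1.11. If the same intra-cluster correlation holds for the tested outcome, an unadjusted standard error is too small by a factor of √1.11 = 1.05.

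**6. Power of the proportion comparison.** The effective number per arm is 120.6/1.11 = 108.6. The pooled standard error is √(2 × 0.24 × 0.76/108.6) = 0.0580, and under the alternative √((0.18 × 0.82 + 0.30 × 0.70)/108.6) = 0.0574. Then (0.12 − 1.96 × 0.0580)/0.0574 = 0.11, which gives power of about 54%.

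**The case against.** The strongest reply is that this is loose drafting. The sentence ends by comparing participants in the two arms and names no subset. The article also uses VLS loosely elsewhere: Role of the health worker applies low VLS to individual children with high viral loads, and Baseline data lists VLS among measurements taken when every child is unsuppressed. On that usage, mean viral load of all participants may be meant. This stands as far as it goes: the restriction to suppressed children is the literal reading, not a certain one. The looser reading still leaves a continuous outcome, a test that ignores clustering, and a conflict with the Abstract and the sample size.

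A reader might go further and infer that the trial, as planned, cannot show whether the Konga model raises suppression. The document does not support that. The Abstract names the proportion suppressed as primary, and Data processing and analysis plans tests of proportions and a regression adjusted for clustering. These are not tied to the primary outcome, but they are planned. The difference-in-difference element changes nothing, since suppression at baseline is 0% in both arms by design.

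It can also be said that the scale of viral load and the handling of missing 6-month values belong in an analysis plan. That is right. The article does not say the t-test would use raw values, so skewness is not held against it here, and no rule for missing values is needed to repair the sentence.

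**Conclusion.** The concern holds as a defect in one sentence and a contradiction across sections. The only analysis that Data processing and analysis ties to the primary outcome fails on either reading. Literally, it selects on the outcome, uses about 22 versus 36 children and rejects about 5% to 10% of the time under the planned effect. Loosely, it is an unclustered t-test of a continuous outcome in a cluster-randomised trial sized on a proportion. Outcome measures adds a third, incompatible primary outcome.

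The counts depend only on the plan's figures. The rejection rates depend on the literal reading and on assumed viral-load distributions without clustering. The mismatch between sections depends on no assumption.

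**What to change.** Replace the sentence in Data processing and analysis. State that the primary analysis compares, by allocated CTC arm, the proportion of all enrolled children with a viral load below 1000 copies/ml at 6 months, using a cluster-adjusted method suited to 20 CTCs. Keep mean log10 viral load in all children as a secondary analysis. Say which outcome the regression and the proportion tests serve. Revise Outcome measures so that viral suppression is primary there too, and give adherence and retention a place consistent with that. Missing 6-month viral loads can be dealt with in the analysis plan.

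The cost is two paragraphs of wording, with no new data; if Outcome measures reflects a considered choice, the investigators must first settle which outcome is primary. The change does not restore the stated 80% power: at 134 per arm the proportion comparison has about 54% (10 clusters per arm, intra-cluster correlation 0.01, 10% loss). The sample size needs separate attention.

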### Study design and population

We will use a cluster-randomized trial study designed with both intervention and control arms. The study will involve 268 children (134 controls and 134 patients who receive intervention) aged 2–14 years who are attending CTC and who have a viral load of >1000 copies/ml.

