**Figure 1: bpac002-F1:**
[figure not shown]
study design and flow chart.

The study will be open-label whereby the Konga, caretakers, and the children will be aware of the intervention received since neither the outcome assessor nor person receiving the intervention will influence the outcome. The study’s primary outcome is to reduce the viral load <1000 copies/ml.

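### As worded, the t-test called primary is confined to children who reach viral suppression, a group formed after randomisation by the outcome itself

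*Protocol article*

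**What the plan says.** All places are in the protocol article.

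- **Data processing and analysis** labels the primary outcome with "As for the primary outcome (mean difference in the viral load of HIV-positive children with VLS". It assigns an independent t-test "to compare the means of participants in the intervention and control arms". The same paragraph plans a multivariable regression adjusted for clustering, and tests of proportions by difference in difference as measures of improvement.
- **Study design and population** enrols children "who have a viral load of >1000 copies/ml". The Abstract repeats this: "The study will involve 268 children with a viral load of >1000 copies/ml who are aged between 2 and 14 years".
- **Dependent variable** says the viral load is "classified as suppression when the count is <1000 copies/ml and unsuppressed when >1000 copies/ml".
- **The text beneath Figure 1** says: "The study’s primary outcome is to reduce the viral load <1000 copies/ml".
- **Sample size calculation and selection** plans "to increase the proportion of children with viral suppression from 18% to 30" per cent, with 134 children per arm and 10% loss. The Abstract also takes the proportion suppressed as primary.
- **Outcome measures** ranks adherence and retention as primary and viral load as secondary.

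**The concern.** The entry criterion and the definition of suppression do not overlap, so the group named in the primary analysis is empty at baseline. It can be filled only by children whose viral load falls below 1000 copies/ml during follow-up, and that fall is the result the intervention aims for. Taken as written, the test compares successes in one arm with successes in the other.

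Two things follow. The suppressed children in the two arms are not the groups that randomisation created, so a difference between them need not be an effect of the intervention. And an intervention that brings more children below the threshold gets no credit for doing so, because the count of successes is not part of the comparison. A log scale, a rank test or an adjustment for clustering would not help, since each leaves the selection in place.

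**Working it through.** **Step 1: when can the analysis set exist?** Entry requires more than 1000 copies/ml (Study design and population). VLS requires less than 1000 (Dependent variable). No child meets both at entry. The End of study section collects viral load at 6 months, and Outcome measures gives baseline and 6 months as its only two time points. The named group is therefore the children suppressed at 6 months.

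**Step 2: how many children is that?** Inputs from the sample size section: 134 per arm, 10% loss, 18% suppressed under standard care, 30% under the intervention.

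- Followed per arm: 134 × 0.90 = 120.6
- Control, suppressed: 120.6 × 0.18 = 21.7, about 22
- Intervention, suppressed: 120.6 × 0.30 = 36.2, about 36
- Total: 57.9, about 58; 57.9 / 268 = 22%, so 78% of enrolled children are outside the test
- Without loss: 134 × 0.18 = 24.1 and 134 × 0.30 = 40.2, total 64.3 of 268, or 24%

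The 268 is used here only as the planned enrolment. It does not reproduce as a total. The unpooled two-sided formula gives 195 per arm. With 10 clinics per arm and an ICC of 0.01, the cluster size is 195 × 0.99 / (10 − 1.95) = 24.0, so 240 per arm, and 240 / 0.9 = 267 per arm. That is a separate matter and does not affect this point.

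**Step 3: what can the t-test detect in this subset?** This is an illustration by simulation. Its assumptions are not in the document: log10 viral load normal, SD 0.8, 1.0, 1.3 or 1.6, means set so that 18% and 30% fall below 1000 copies/ml, values floored at 20 copies/ml, 121 children per arm, no clustering, 4000 runs per case. In every case the planned effect on suppression is exactly present.

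| Where suppressed children's viral loads fall | Rejection rate | Direction |
|---|---|---|
| Same distribution in both arms | about 5% | none; the false-positive rate |
| Uniform log10 shift in every child | about 8–9% | mainly favours intervention |
| Extra responders at 200–999 copies/ml | about 10–30% | almost always against intervention |
| Extra responders at 20–200 copies/ml | about 20–47% | almost always favours intervention |

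The same true effect on suppression gives anything from no signal to a signal in either direction. What decides it is the extra responders' viral loads, on which the document is silent.

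**Step 4: the comparison that keeps all followed children.** With 120.6 per arm in 10 clinics, the cluster size is 12.06 and the design effect is 1 + 11.06 × 0.01 = 1.1106. The effective size is 120.6 / 1.1106 = 108.6 per arm, and power for 18% versus 30% is about 54%. The gap to 80% comes from the sample size. This comparison does test the planned contrast directly.

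**The case against.** The strongest reply is that the qualifier is a slip. The t-test clause in the same sentence speaks of participants in the two arms, without limiting them to suppressed children. The Abstract has a nearly parallel sentence about the proportion suppressed, where a reference to suppression belongs; the analysis section may be that sentence with the proportion replaced by a mean and the qualifier left behind. The article also uses VLS loosely: the Baseline data section lists it among the items to record, although no enrolled child is suppressed then. Nowhere does the article describe discarding unsuppressed children, and viral load is collected in both arms at 6 months.

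This makes a slip plausible, but it does not settle the analysis set. The parenthesis is what defines the outcome, and no other sentence says which children enter this t-test. Nor is it a detail left to a fuller document, because the article states a specific analysis and names the wrong group.

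Two stronger readings are tempting. A reader might infer that the trial cannot show an effect on suppression at all. The document does not support that: the Abstract and the analysis section both plan tests of proportions, and a clustered regression is planned as well. A reader might also infer that the restricted test would make a useful intervention look harmful. That holds only if the extra responders land just under the threshold; if they land low, the bias runs the other way.

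**Conclusion.** The point stands as a defect of wording in the stated primary analysis. Read literally, the t-test uses about 58 of 268 children (22%), selected by the outcome, and the 18% versus 30% contrast is removed from it. The structural part needs only the entry criterion and the definition of suppression. The count also needs the plan's own suppression rates and loss. The rejection rates rest on assumed viral-load distributions and show only that the direction of any remaining difference is undetermined.

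The defect is confined to this t-test. Whether the authors meant to restrict the set cannot be determined from the article, but the sentence should be corrected either way, because the article labels this comparison as primary and describes the tests of proportions only as measures of improvement.

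**What to change.** In Data processing and analysis:

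1. Delete the qualifier that limits the primary comparison to children with VLS.
2. State the viral-load primary analysis as the proportion below 1000 copies/ml at 6 months, compared between arms in all children of the randomised clinics, as the Abstract and the sample size section have it, with the clustering adjustment the plan already mentions.
3. If viral load is also compared as a continuous measure, include every child with a 6-month value, suppressed or not.
4. Report viral load among suppressed children as description only, with no test between arms.

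Reconcile this with Outcome measures, which ranks viral load as secondary, so that one primary outcome is named throughout.

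The cost is a change of wording. No further data or children are needed, since the 6-month viral load is already to be collected in both arms.

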### Selection and randomization of CTC

A site assessment will be performed before the final site selection and sites will be selected to participate in the study based on infrastructure feasibility, last numbers of children enrolled into CTC during the past year, numbers and qualification of staff affiliated to CTC and balanced representation of the different level of health facilities and urban versus rural affiliations. Assignment of sites to one of the two study arms will be done by randomization (Fig. 1). Stratification during the randomization process (e.g. rural versus urban) will be considered.

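### Clinics are randomised, but the test named for the primary outcome treats children as independent, and the planned cluster-adjusted regression is not said to govern the conclusion

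*Protocol article*

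**What the plan says.** **Design.** The Study design and population section states: "We will use a cluster-randomized trial study designed with both intervention and control arms". The Selection and randomization of CTC section confirms the unit: "Assignment of sites to one of the two study arms will be done by randomization". The Sample size calculation and selection section gives the numbers: "10 CTCs will carry out the intervention and 10 CTCs will carry out standard care". It plans 268 children (134 per arm), an ICC of 0.01, 80% power, a 5% significance level and 10% loss to follow-up.

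**Analysis.** In the Data processing and analysis section, the method attached to the primary outcome (there worded as a mean difference in viral load) is an independent t-test, a "test to compare the means of participants in the intervention and control arms". The next sentence reads: "We will develop a multivariable regression model, adjusting for clustering and other confounders for potential confounding". After that come tests of proportions with a difference-in-difference, and a two-sided 0.05 threshold for every test.

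**Abstract.** The primary comparison is of suppression proportions between arms: "Proportions and tests for different proportions will be used as a measure of improvement". Clustering is not mentioned in the analysis sentences. The abstract calls the design cluster-randomised but also says: "The children will be randomly allocated into the intervention and control arms".

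**The concern.** When clinics are randomised, the arm difference varies for two reasons: children differ, and clinics differ. A t-test or test of proportions on individual children counts only the first source. If outcomes are positively correlated within a CTC, the standard error is too small and the test rejects a true null hypothesis more often than its nominal level.

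The protocol accepts this correlation when it sizes the trial, then names a primary-outcome test that assumes there is none. This goes beyond detail that a short article leaves to a fuller document, because a specific test is named and it does not match the design. If that test carries the conclusion, the stated 5% threshold is not held, and the error runs towards declaring benefit or harm where there is none. If the t-test and the regression disagree, nothing in the text says which one decides.

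**Working it through.** **Inputs from the Sample size calculation and selection section.** 134 children and 10 CTCs per arm; ICC 0.01; 10% loss; control suppression 18%. The two-sided 5% level is also in the Data processing and analysis section.

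**The plan's own figure.** The stated total of 268 does not follow from the stated inputs. For 18% against 30%, with 80% power and two-sided 5%, about 198 per arm are needed before clustering. With 10 CTCs per arm: 198 × 10 × 0.99 / (10 − 198 × 0.01) = 244 per arm, and 244.4 / 0.9 = 272 after loss. That is a separate issue. Here 134 per arm is taken as the planned size.

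**Formulas.** With m children per CTC:
- Design effect: DE = 1 + (m − 1) × ICC
- Factor by which the child-level standard error is too small: √DE
- True type I error of a nominal 5% child-level test: 2 × [1 − Φ(1.96 / √DE)]

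**At the plan's ICC, full enrolment.** m = 134 / 10 = 13.4. DE = 1 + 12.4 × 0.01 = 1.124. √1.124 = 1.060. Type I error = 2 × [1 − Φ(1.96 / 1.060)] = 6.45%.

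**At the plan's ICC, after 10% loss.** m = 120.6 / 10 = 12.06. DE = 1 + 11.06 × 0.01 = 1.111. √DE = 1.054. Type I error = 6.3%.

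**Other ICCs (assumptions, not in the protocol), by formula.**

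| ICC | m | DE | √DE | Type I error |
|---|---|---|---|---|
| 0.01 (plan) | 13.4 | 1.124 | 1.060 | 6.45% |
| 0.05 | 13.4 | 1.62 | 1.273 | 12.4% |
| 0.10 | 13.4 | 2.24 | 1.497 | 19.0% |
| 0.05 | 12.06 | 1.553 | 1.246 | 11.6% |
| 0.10 | 12.06 | 2.106 | 1.451 | 17.7% |

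**Check by simulation.** Beta-binomial data, 10 CTCs per arm, null suppression rate 18%, 200,000 replicates:

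| Children per arm | ICC | Child-level test | t-test on CTC proportions, 18 df |
|---|---|---|---|
| 134 | 0.01 | 6.5% | 5.0% |
| 134 | 0.05 | 12.5% | 5.0% |
| 134 | 0.10 | 19.2% | 4.9% |
| 120 | 0.01 | 6.5% | 5.0% |
| 120 | 0.05 | 11.8% | 4.9% |
| 120 | 0.10 | 18.0% | 4.9% |

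The formula and the simulation agree, and the cluster-level test holds its level throughout.

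**Limit of these figures.** They apply to the suppression proportion, the outcome for which the ICC of 0.01 is stated. The t-test is on mean viral load, for which no ICC is given. Its outcome is also worded as viral load among children with suppression. Read literally, only 18–30% of 13.4, or about 2.4–4.0 children per CTC, would enter. If ICC 0.01 applied there (an assumption), DE would be 1.01–1.03 and the type I error about 5.2–5.4%. At ICC 0.05 it would be about 5.8–6.8%.

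**The case against.** The strongest reply is that the plan does deal with clustering. The sentence after the t-test promises a regression that adjusts for it, and nothing labels that model secondary. A simple comparison followed by a cluster-adjusted model is a fair reading. This stands in part: a reader might infer that the plan ignores clustering altogether, and it does not. But the regression is a separate step with no named outcome, and it is not said to replace the t-test, which is the method attached to the primary outcome.

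The second reply is that the distortion is small at the plan's own ICC, about 1.5 percentage points. That stands. Error rates of 12% or more depend on ICCs that the protocol does not contain.

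Some stronger readings are tempting but unsupported:
- That planned confidence intervals will be too narrow. The article plans none, although any built on the same standard error would be.
- That the chi-squared and Fisher tests are invalid outcome tests. They are named for univariate analysis and are not tied to the between-arm outcome comparison.
- That the regression will use standard errors too small for 20 clusters. No estimation method is named, and that detail may properly sit elsewhere. A small-sample correction belongs in the remedy.
- That children are individually randomised. The abstract's sentence is loose wording, since the same abstract calls the design cluster-randomised.

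**Conclusion.** The point holds in a limited form. The test attached to the primary outcome does not match the unit of randomisation, and the between-arm test of proportions is not described as cluster-adjusted. The one analysis that allows for clustering is not made decisive.

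For the suppression proportion at the protocol's ICC of 0.01, a nominal 5% child-level test has a type I error of about 6.5% (6.3% by formula after 10% loss). This assumes equal or near-equal numbers per CTC. If the ICC were 0.05 or 0.10, the figure would be about 12% or 18–19%; these show sensitivity and are not predictions. For the t-test on mean viral load, the direction follows from any positive ICC, but the size cannot be established from the document.

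**What to change.** State in the Data processing and analysis section that the primary between-arm inference comes from one cluster-aware analysis, and name it. Either option suits 20 clusters:

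1. A t-test on the 20 CTC-level summaries (proportion suppressed, or mean, according to the primary outcome), with 20 − 2 = 18 degrees of freedom.
2. The regression already planned, specified as a mixed or GEE model with CTC as the cluster and a small-sample correction, and explicitly tied to the primary outcome.

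Do not use the unadjusted t-test or test of proportions for between-arm outcome inference. Correct the abstract to say that CTCs are randomised. The outcome wording also needs to be settled, because the sections describe the primary outcome differently. The requirement for a cluster-aware test is the same whichever is confirmed.

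The cost is a change of wording, with no new sites or data. Standard errors would be about 6% larger than the child-level ones at ICC 0.01. They would be about 27% or 50% larger if the true ICC were 0.05 or 0.10 (√DE = 1.273 and 1.497 at 13.4 children per CTC).
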